### **Instructions to DSMB: Stopping Rules/Guidance**

- Thus, if the Z statistic is greater than 2.834 at the interim analysis, the committee will then consider that there is statistical evidence for overwhelming efficacy.
- The committee should then consider the primary outcome analysis using the ordinal logistic regression (proportional odds model).
- Next the committee should consider any effect upon all-cause mortality
- Finally the committee should consider the treatment effect in two subgroups: patients treated with IV tPA and patients not treated with IV tPA.

**The committee is then entrusted with a decision to make recommendations about the continuation of the trial in the context of the data and the context of the current and known evidence about endovascular stroke treatment using their best judgment.**

Because of past experience with IMS-3 and published results from the Penumbra, SWIFT and TREVO trials, we have confidence in the safety of endovascular treatment. However, as has evolved in past trials of hemicraniectomy in stroke, and in the SWIFT trial, there is a possibility that mortality in the control group may be higher than the treatment group, even when a morbidity benefit is not evident. Because our objective is to demonstrate a morbidity benefit, the DSMB will be asked to consider such a result (mortality benefit) carefully before recommending that the trial continue or be halted. This will be facilitated by having stringent futility and overwhelming efficacy boundaries using O'Brien-Fleming methods (which are known to be conservative at the interim analysis stage). There will be no analysis for futility.

### **5. Definition of the target population**

#### **5.1. Efficacy population**

All patients enrolled in the trial randomized on an intent-to-treat basis.

#### **5.2. Safety population**

All patients enrolled in the trial who received the intervention, for the endovascular group. All patients in the control group who received best standard of care.

## 6. Randomization

Randomization will be managed using a custom SQL server-based database that will instantly and dynamically assign treatment using the minimal sufficient balance algorithm. Randomization will therefore be conducted over the internet via a desktop computer or a web-enabled smart phone.

Randomization will be 1:1. Allocation will be 1:1 set at  $p(0.5)$  for the first 40 patients. Thereafter, a minimization algorithm (minimal sufficient balance) will be utilized to ensure ongoing balance in the trial on the following factors:

- Age

- Baseline NIHSS score

- Sex (male or female)

- Baseline ASPECTS score, dichotomized as 6-7 or 8-10.

- Intracranial occlusion location, dichotomized as MCA or ICA.

- IV tPA use (yes or no)

The minimal sufficient balance (MSB) randomization is a minimization procedure that preserves balance in smaller trials, such as this one, where imbalances in important baseline prognostic variables may occur by chance and confound the primary outcome. In addition, it preserves a greater degree of randomness in patient allocation compared to permuted block designs. Because of the MSB process, randomization assignments will be stochastically derived in real time using a interactive web-site and therefore concealment can never be breached. Allocation will be open.

Reliance on a process that requires real-time data entry makes the process susceptible to error. For example, incorrect information (eg. wrong sex or incorrect site of occlusion) could be mistakenly entered into the randomization process and affect the minimization algorithm. Post-hoc, when such errors become known, the quality-controlled database entry will be considered the source of truth and the randomization database will be updated to ensure that ongoing randomization utilizes the most correct data to determine balance in an ongoing way.

The randomization process is not blocked, nor stratified by site. Therefore, the number of patients enrolled into each arm of the study may not be exactly even at the time the study is completed. The proportion of patients enrolled into each arm at each site may also vary and not be equally distributed. These decisions were taken explicitly with the knowledge and belief that balance on 6 key patient characteristics in the trial overall are more important than balance by site.

## 7. Blinding

Treatment assignment is open-label. Blinding of the outcome assessment at 90 days will be ensured at the site by having a person who was not involved in the acute treatment period conduct the assessment.

## 8. Missing data

Under the ITT principle, all patients who are randomized are included in the analysis. Therefore, missing data, especially in the outcome measures, can be problematic. Thus every effort will be made to keep all missing data to a minimum. In the event that, despite the clinical centers' best efforts, there are missing data, then for the primary outcome analysis, missing outcome data will be imputed by assuming the missing mRS score at 3 months to be unfavorable. We will assign the worst possible score. If the patient is known to be alive, we will impute a score of 5. If the patient is not known to be alive or dead, we will impute a score of 6.

Furthermore, if the assessment was conducted outside of the protocol-specified time window, data obtained are still included in the analysis, with the rationale that it is a more accurate measure than those obtained by imputation. At a minimum 90-day outcome assessments will be accepted within a +/- 30-day window.

For sensitivity analysis, the missing outcome values will be imputed using the following methods:

- If one-month or 5-day/discharge outcome scores are available, carry forward those values; else, assume the worst case.
- Assign failure (worst possible score) to all subjects with missing 3-month outcome data.
- Multiple imputation method based on the regression model
- Hot-deck or nearest neighbor method, using clinical site, age, sex, baseline NIHSS, baseline serum glucose, baseline ASPECTS, IV tPA use, treatment group as classification variables.
- Regression method, with age, sex, baseline NIHSS, baseline serum glucose, IV tPA vs. non-IV tPA, and treatment group as covariates.
- In the endovascular group, impute values for LTFU with failure (worst possible score), and in the control group, with success (the best-worst case imputation) in the intervention group.

Similar imputation methods will be employed for secondary categorical outcomes. For the raw NIHSS score, multiple imputation, regression, and mean substitution methods will be used in the sensitivity analyses. Missing covariate data, if any, will be imputed using either multiple imputation or regression method, if needed.

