### 3. Sample size

There is now empirical evidence that the mRS scale, when categories 5 and 6 are combined, is a truly interval scale meaning that the difference in utility (or function) between any one step increment in the scale is the same; thus, it is unlikely that the proportional odds assumption will be violated. The trial is powered to detect a statistically significant shift in the distribution of scores on the mRS scale at 3 months between the treatment and the control arm, assuming that categories 5 and 6 (bedbound with severe disability, and death) are collapsed into one category, and the effect leads to an assumed common odds ratio of 1.8. The expected distribution of outcomes is based upon the pooled experience from the literature [SWIFT study, STAR registry, Calgary data, IMS-3 study limited to an ESCAPE population, ALIAS part 1 study limited to an ESCAPE population] and a 5% increase in favourable outcome per mRS category. [Figure 1] In IMS-3 there was an average 2% non-significant improvement in favourable outcomes per mRS category; in SWIFT (which compared two endovascular devices), there was an average 8% improvement in favourable outcomes per mRS category. Using Calgary data, the common OR for improvement across the mRS scale with endovascular treatment compared to IV only was 2.1 (CT95 1.1-4.2). [[name], unpublished data]

A total sample size of 188 patients per group is required for 90% power, two-sided alpha at 0.05 and 1:1 randomization to detect a common OR of 1.8, based upon the expected distribution shown below (figure 1). The sample size calculation is based upon Whitehead's power formula. The sample size is estimated without knowing the distribution of pre-specified confounding variables. We assume no cross-overs. Allowing for losses-to-follow-up (of up to 6%, n=24/400), a total required sample size of 400 ideal patients is anticipated. However, we know that the effect size is highly dependent upon very rapid treatment times and have planned to continue enrolling patients until up to 200 endovascular patients have been treated with a CT-to-first reperfusion time < 90 minutes. Currently, in our initial patients we are meeting this quality metric in 60% of our patient population, compared to our desired 80% or greater. We conservatively assume that the effect size is absent if we do not achieve our target treatment times. Therefore,

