## 9.2. Secondary analyses

Pre-specified secondary outcome and safety analyses of proportions will be conducted in a similar way to the primary analysis using logistic regression or using a multivariable generalized linear model with log link to derive risk ratios directly. Pre-specified secondary analyses will include the following:

- 9.2.1. Adjusted analysis on the primary outcome using key stratifying variables from the MSB algorithm (age, sex, tPA use, ASPECTS score, NIHSS score, occlusion location)
- 9.2.2. Adjusted analysis using other known predictors of outcome after stroke (6 variables above, time, serum glucose, atrial fibrillation, ipsilateral carotid artery stenosis/occlusion, diabetes mellitus, blood pressure at baseline, miFUNCTION score)
- 9.2.3. Dichotomized outcome on the 90-day: mRS (independent 0-2 vs. dependent 3-6), the NIHSS 0-2 vs. 2-42, Barthel index 95-100 vs. 0-90, mortality. Each dichotomized outcome will be modeled as a function of key covariates (as per 8.2.2) using logistic regression model. The odds ratio and the corresponding 95% confidence interval for each covariate will be reported
- 9.2.4. Reperfusion and recanalization analysis based upon angiographic data (endovascular group) and CTA data (control group). Proportion of patients with early recanalization, extent of recanalization.
- 9.2.5. Analysis of the role that time from onset and time from CT imaging plays in predicting outcome defined by the mRS by group.
- 9.2.6. Analysis on the primary outcome using baseline imaging as a stratifying variable (ASPECTS 8-10 vs. 5-7, multi-phase CTA collaterals good vs. intermediate and perfusion CT small vs. intermediate infarct core) Simple effects and interactions will be considered in this analysis.
- 9.2.7. Analysis of quality of life, measured using the EuroQOL. We will report the unadjusted distribution by group.
- 9.2.8. Economic analysis will be conducted using Canadian hospital data and quality of life measure to estimate treatment utility.

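### The sample size treats lost patients as dropped, but the primary analysis scores them worst: at the planned maximum 6% loss, power is about 86%, not 90%

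*SAP*

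**What the plan says.** Section 3 (Sample size) gives the target: "A total sample size of 188 patients per group is required for 90% power, two-sided alpha at 0.05 and 1:1 randomization". The effect is a common odds ratio of 1.8 on the 3-month mRS with categories 5 and 6 collapsed, and the method is Whitehead's. The allowance for loss follows: "Allowing for losses-to-follow-up (of up to 6%, n=24/400), a total required sample size of 400 ideal patients is anticipated".

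Section 8 (Missing data) includes all randomized patients in the primary analysis and replaces a missing 3-month mRS by the worst score. A patient known to be alive receives 5. For the rest: "If the patient is not known to be alive or dead, we will impute a score of 6". Carry-forward, multiple imputation, hot-deck, regression and a best-worst case appear only as sensitivity analyses. That list also contains: "Assign failure (worst possible score) to all subjects with missing 3-month outcome data".

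After the list, section 8 adds: "Similar imputation methods will be employed for secondary categorical outcomes". Section 9.2.3 names the dichotomized 90-day outcomes, among them "Barthel index 95-100 vs. 0-90, mortality". No sentence says whether mortality is exempt from imputation.

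**The concern.** Sections 3 and 8 make different assumptions about the same patients. Dividing by 0.94 is right when lost patients leave the analysis: the sample shrinks and the effect among those remaining is unchanged. Under section 8 the sample does not shrink, but a fixed share of each arm sits in the worst category whatever the treatment did. That pulls the two distributions together, and the sample size contains no allowance for it.

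Two things are at stake. First, the stated power is not delivered at the stated maximum loss. Second, the rule is not reliably conservative. If loss differs between arms, which is possible in an open-label trial, the arm with less loss looks better even when treatment does nothing.

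Two smaller points follow from the same section. The sentence on secondary categorical outcomes can be read to let patients of unknown vital status count as deaths in the mortality analysis. And one of the listed sensitivity analyses hardly differs from the primary rule.

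**Working it through.** **Inputs from SAP section 3:** common odds ratio 1.8, two-sided alpha 0.05, power 90%, 1:1 allocation, six categories (5 and 6 collapsed), loss up to 6%, 400 patients. **Assumed:** the mRS distribution, because Figure 1 is not shown. Five distributions were tried.

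**1. Reproducing the plan's figure.** Whitehead: n per arm = 6(z₀.₉₇₅ + z₀.₉₀)² / {(ln OR)² (1 − Σp̄³)}, where p̄ are the category proportions averaged over arms. With six equal mean categories, Σp̄³ = 6 × (1/6)³ = 0.0278, so n = 6 × (1.960 + 1.282)² / (0.5878² × 0.9722) = 187.7, that is 188. The other four distributions give 188.4 to 192.1. Then 376/0.94 = 400. The stated figures reproduce.

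**2. Power under section 8.** Each arm's distribution p becomes 0.94p with 0.06 added to the worst category, at 200 per arm. The proportional odds model is refitted to the diluted distributions, and power is Φ(√[n(ln OR)²(1 − Σp̄³)/6] − 1.960). In the equal-category case the odds ratio is 1.705 and Σp̄³ = 5 × 0.1567³ + 0.2167³ = 0.0294. The root is √(200 × 0.5336² × 0.9706/6) = 3.035, and Φ(1.075) = 0.859. The simulation column is the tie-corrected Wilcoxon test (the proportional odds score test), 40,000 replicates.

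| Control distribution, best to worst (%) | n per arm, step 1 | OR at 6% loss | Power, formula | Power, simulated | n per arm for 90% |
|---|---|---|---|---|---|
| equal mean categories | 187.7 | 1.705 | 85.9% | 85.5% | 229 |
| 7/11/12/16/22/32 | 189.5 | 1.721 | 86.5% | 86.3% | 225 |
| 10/13/13/15/19/30 | 188.6 | 1.718 | 86.5% | 86.3% | 224 |
| 8/12/15/18/20/27 | 188.4 | 1.714 | 86.3% | 86.0% | 226 |
| 8/10/12/15/15/40 | 192.1 | 1.732 | 86.7% | 86.3% | 223 |

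Dropping the lost patients (188 per arm) gives 89-90%. With worst-score imputation, power is about 90% at 2% loss, 89% at 3% and 88% at 4%. Restoring 90% at 6% loss would take 223-229 per arm, or 446-458 in total. An uncollapsed seven-category example, with every lost patient scored 6, gives 85.8%.

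**3. Unequal loss with no true effect.** Let q be the true share in the worst category, the same in both arms. With 8% loss in control and 4% in endovascular, the difference between the chance that an endovascular patient does better and the chance that a control patient does better is (0.08 − 0.04)(1 − q). Its standard error is √[(2/(3 × 200))(1 − Σp̄³)].

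- q = 0.32 (second row): difference 0.0272, standard error 0.0559, ratio 0.486. The chance of Z > 1.96 is 1 − Φ(1.474) = 7.0%.
- q = 0.207 (first row's control arm): difference 0.0317, standard error 0.0567, ratio 0.559. The chance is 1 − Φ(1.401) = 8.1%.

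The nominal value is 2.5%. With the split reversed the chances are 1 − Φ(2.446) = 0.7% and 1 − Φ(2.519) = 0.6%.

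**4. Mortality, if unknown status were scored as death.** At loss l, all of unknown status, true mortality m becomes (1 − l)m + l. Assumed rates of 20% and 15% become 0.94 × 0.20 + 0.06 = 24.8% and 0.94 × 0.15 + 0.06 = 20.1%. The risk ratio moves from 0.75 to 0.81. False deaths per 200 at 15% mortality would be 200 × 0.06 × 0.85 = 10.2.

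**The case against.** The best defence is that worst-score imputation is pre-specified, transparent and free of any missing-at-random assumption. Section 8 also lists several alternatives, including a case scoring endovascular losses as failures and control losses as successes, which tests the direction of bias that matters most. All of that stands. It means the choice of method is defensible; it does not make the sample size agree with it.

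The 6% is an upper limit, and at 2-3% loss the shortfall is a point or so. That also stands: 86% belongs to the ceiling the plan itself sets.

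A reader might infer more than the SAP supports:

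- *That all lost patients become deaths.* Those known alive receive 5. With 5 and 6 collapsed, the choice between them has no effect on primary power; the loss comes from the worst-category rule.
- *That mortality will contain invented deaths.* The sentence on secondary outcomes follows the sensitivity list and may refer only to those methods. The text is ambiguous.
- *That the DSMB would see such deaths.* Section 4 bases the interim looks on patients who have completed 3-month follow-up, and nothing puts imputed deaths into that review.
- *That all 12 lost patients per 200 would be false deaths.* Some would truly have died; the figure is about 10 at 15% mortality, and only if all have unknown status.
- *That the bias runs towards endovascular treatment.* The 8%/4% split is assumed, and the reverse split makes such a result rarer than nominal.
- *That the worst-score sensitivity analysis is an exact duplicate.* It is identical only if 5 and 6 are collapsed, which section 3 states for powering and section 9.1 does not repeat. Otherwise it moves known-alive patients from 5 to 6.

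Nor does the enrolment limit of 500 close the gap. Section 3 provides it to reach 200 endovascular patients within target treatment times, and assumes no effect where those times are missed.

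**Conclusion.** The mismatch between sections 3 and 8 is real. At the plan's maximum of 6% loss in each arm, with 400 ideal patients and a true common odds ratio of 1.8, power is about 86% (85-87%) rather than 90%; at 3% loss it is about 89%. The result rests on an assumed mRS distribution but barely depends on it.

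The risk from unequal loss is also real, but its size and direction depend on a split that the SAP does not give. The mortality point is a request for clarity. The overlapping sensitivity analysis is minor.

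**What to change.** - **Power.** State in section 3 that under the primary imputation rule power is about 86% at 6% loss and about 89% at 3%. This costs a sentence.
- **Optional alternative.** Make the multiple imputation already listed in section 8 the primary method, with treatment arm, the minimization variables and the 5-day/discharge and one-month scores as predictors, and keep worst-score imputation as a sensitivity analysis. This costs some programming. The primary result would then rely on missing-at-random given those predictors. It is a trade-off, not a required correction.
- **Mortality.** State that mortality uses observed vital status and that no death is imputed for a patient of unknown status. Report the number of such patients by arm, because the analysis then leaves them out.
- **Sensitivity list.** Remove or replace the analysis assigning the worst score to all missing patients, and say in section 9.1 whether 5 and 6 are collapsed in the primary model.

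Section 9.1 allows the plan to be revised before the blind is broken, so each change can be made as an ordinary amendment.

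### One of the six missing-outcome sensitivity analyses repeats the primary rule, and the only opposite-extremes analysis contradicts itself on which arm gets the good outcome

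*SAP*

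**What the plan says.** The primary rule in SAP section 8 is "We will assign the worst possible score". It is then made specific: "If the patient is known to be alive, we will impute a score of 5", and "If the patient is not known to be alive or dead, we will impute a score of 6".

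Six sensitivity methods follow:

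1. "If one-month or 5-day/discharge outcome scores are available, carry forward those values; else, assume the worst case".
2. "Assign failure (worst possible score) to all subjects with missing 3-month outcome data".
3. "Multiple imputation method based on the regression model".
4. Hot-deck or nearest-neighbour imputation.
5. Regression imputation.
6. An opposite-extremes analysis. It gives failure to endovascular patients lost to follow-up and success to control patients, but the control clause ends "with success (the best-worst case imputation) in the intervention group".

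On the scale, section 3 powers the trial "assuming that categories 5 and 6 (bedbound with severe disability, and death) are collapsed into one category". Section 9.1 specifies a proportional odds model for the mRS without repeating the collapse. Its fallback, if proportional odds fails, is mRS 0-2 against 3-6. Section 3 allows for loss to follow-up of up to 6% (24 of 400).

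**The concern.** A sensitivity analysis is informative only if it could give a different answer from the primary analysis. The second method uses the same phrase as the primary rule and, on the scale used for powering, cannot differ from it. Listing the agreement as support for the primary result would overstate how much had been checked.

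The sixth method is the only one that pushes the two arms in opposite directions. Treatment is open-label, so loss to follow-up could differ between arms in amount or in kind, and an arm-specific extreme case addresses exactly that. Its sentence names control and then the intervention group as the arm receiving success, so it cannot be programmed literally. The two directions are a severe test of the treatment effect and a very lenient one.

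**Working it through.** **Inputs from the SAP (section 3).** Common OR 1.8, two-sided alpha 0.05, power 90%, 188 per group, loss up to 6%, total 400.

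**Assumptions.** Figure 1 is not shown, so the mRS distribution is assumed. For the fitted odds ratios, control mRS 0 to 6 is 10/12/13/15/20/10/20%. Success is taken as mRS 0 and failure as the worst category.

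**Step 1: reproduce the plan's sample size.** Whitehead's formula is n per group = 6(z₀.₉₇₅ + z₀.₉₀)² / [(ln OR)² (1 − Σp̄³)].

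- With six equal categories, 1 − Σp̄³ = 1 − 6 × (1/6)³ = 0.9722.
- 6 × (1.960 + 1.282)² / (0.5878² × 0.9722) = 187.7, which rounds up to 188.
- Three skewed six-level distributions give 188 to 189.
- 2 × 188 / 0.94 = 400.

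The plan's figures reproduce, and 6% of 200 is 12 missing per arm.

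**Step 2: second sensitivity method against the primary rule.** A proportional odds model was fitted to expected counts: 188 observed per arm at OR 1.8, plus the imputed patients. For the seven-level fits, the second method is read as a 6 for everyone. The range for the primary rule runs from no missing patient known alive to all of them known alive.

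| Missing endovascular / control | Scale | Primary rule, OR | Second method, OR |
|---|---|---|---|
| 12 / 12 | 5 and 6 collapsed | 1.718 | 1.718 |
| 12 / 12 | seven levels | 1.705 to 1.733 | 1.705 |
| 6 / 18 | 5 and 6 collapsed | 1.971 | 1.971 |
| 6 / 18 | seven levels | 1.982 to 1.931 | 1.982 |

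On the mRS 0-2 fallback, both rules give a difference of 13.4 percentage points with 12 missing per arm: (0.4922 × 188)/200 − (0.35 × 188)/200 = 0.463 − 0.329. If the worst possible score in the second method carries the 5-or-6 definition of the primary rule, the two coincide on seven levels as well.

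**Step 3: the two directions of the sixth method** (5 and 6 collapsed; z is the signed square root of the likelihood-ratio statistic).

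| Missing endovascular / control | Endovascular worst, control best | Endovascular best, control worst |
|---|---|---|
| 12 / 12 | OR 1.27, z 1.33 | OR 2.32, z 4.71 |
| 6 / 18 | OR 1.25, z 1.28 | OR 2.30, z 4.66 |

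**Step 4: how often each direction is significant for endovascular.** Trials of 200 per arm were simulated on six levels with a rank test, at two-sided 0.05, over three assumed control distributions.

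| Loss in each arm | True OR | Endovascular worst, control best | Endovascular best, control worst |
|---|---|---|---|
| 6% (12 of 200) | 1.8 | about 22-25% | 99.8-99.9% |
| 2% (4 of 200) | 1.8 | about 75% | about 97% |
| 6% | 1.0 | close to 0 | 37-40% |
| 2% | 1.0 | below 1% | about 8% |

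**The case against.** Several stronger readings are tempting, and the SAP does not support them.

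- **A reader might infer that the sensitivity set as a whole cannot test the primary rule.** It can. Carry-forward, multiple imputation, hot-deck and regression imputation each replace the 5-or-6 rule with something different. Nor is there evidence that only the opposite-extremes analysis could overturn the result.
- **A reader might take the duplication as unconditional.** It is exact on the collapsed scale and on the binary fallback. Section 9.1 does not restate the collapse, and separating 5 from 6 in section 8 has an effect only if the levels are kept apart. On seven levels the two rules can differ slightly.
- **A reader might infer that the sixth method is written equally in both directions.** Its explicit clauses assign each arm once, endovascular to failure and control to success. The closing phrase looks like an editing remnant, and no clause assigns failure to control. The conservative reading is the more natural one, but the sentence still contradicts itself.
- **A reader might infer that the direction will be picked after the data are seen, or that 37-40% is a type I error of the trial.** The first is conjecture: section 9.1 allows the plan to be revised and finalized before unblinding. The second is wrong, because the sixth method has no role in the trial's decision.

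It is also fair to say that a redundant line biases nothing, that 6% is the plan's ceiling rather than its expectation, and that a tipping-point analysis is a choice the SAP is not obliged to make. All of this limits the weight of the point. None of it removes the empty check or the contradictory wording.

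**Conclusion.** Two defects in section 8 stand, both minor and both curable by wording. The second sensitivity method adds no information on the scale used for powering or on the mRS 0-2 fallback, and next to none on seven levels. The sixth method contradicts itself about which arm receives success, and the direction can decide what it shows: at 6% loss in each arm and a true OR of 1.8, it separates a usually non-significant result from an almost certainly significant one. The gap narrows considerably at 2% loss.

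The redundancy follows from the text alone. The odds ratios and percentages depend on assumed mRS distributions, on equal loss in the two arms for the simulated chances, and on taking success as mRS 0. The primary analysis and its error rate are unaffected.

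**What to change.** 1. State in section 9.1 whether mRS 5 and 6 are collapsed in the analysis, as they were for powering.
2. Replace the second sensitivity method with an arm-specific tipping-point analysis: shift the imputed scores separately by arm and report where significance is lost.
3. Reword the sixth method as: missing endovascular = worst category, missing control = mRS 0. Delete the closing reference to the intervention group. If the reverse is wanted, list it separately and label it only as the opposite bound.

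The cost is a few lines of SAP text and code and one extra sensitivity table. Section 9.1 already allows a revision before the blind is broken.
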